#### Safety

Safety will be determined from adverse event reporting. SAE categories and adverse events of special interest are detailed in Textbox 2. SAEs will be classified by event category, the outcome of the event, the relationship to the study, and by whether they were planned or unplanned. The relationship of the SAE to the study will be determined by medical review. All adverse events will be monitored and recorded via the REDCap research management system throughout the study [29]. In addition, all participants will be asked by a member of the research staff at the end-of-program assessment whether any unreported SAE or adverse event had occurred during the study period.

List of serious adverse events and adverse events of special interest to be recorded and monitored during the study period.
**Serious adverse event categories [32]**
DeathLife-threatening eventHospitalization (acute or prolonged), including planned admissionsEvent resulting in persistent or significant disability or incapacityImportant medical event (eg, adverse drug reaction)Pregnancy
**Adverse events of special interest [32]**
Hypoglycemic episode requiring assistance from another individualFallMusculoskeletal injury requiring medical or allied health attentionHyperkalemia (newly diagnosed or requiring intervention)Episode of low blood pressure requiring medical attentionChest pain requiring medical attention

### Secondary Outcomes

The secondary outcomes that will be evaluated are clinical effectiveness (including metabolic syndrome severity, dietary quality, physical activity and sedentary behavior, exercise capacity, neuromuscular fitness, muscular pain, clinical parameters, quality of life, nutrition and physical activity self-efficacy, fatigue, and sleep quality and quantity), patient-led goal attainment, treatment fidelity, exposure demand, and participant perceptions (Table 2).

#### Clinical Effectiveness

All clinical effectiveness data will be collected at baseline and end-of-program assessments.

##### Metabolic Syndrome Severity Score

The metabolic syndrome severity score (MetSSS) is a continuous risk assessment score for quantifying severity of the MetS. It will be calculated using an algorithm developed from an Australian population that includes systolic blood pressure, diastolic blood pressure, waist circumference, and fasting blood measures (triglycerides, high-density lipoprotein cholesterol, and glucose) [31].

##### Dietary Quality

Habitual dietary intake of the participants will be collected via a 3-day self-administered diet record (2 weekdays and 1 weekend day) using the Research Food Diary mobile app (Xyris Software [Australia] Pty Ltd) [33]. Participants will be asked to record information on the type, portion, and brand of all consumed foods. This includes condiments, oils, herbs and spices, and beverages. The app is blinded such that participants cannot access any nutrient or composition information of foods. Participants will be asked to send their diet record data via the email function, and it will be verified via phone by a study dietitian before analysis. FoodWorks 10 Professional (Xyris) will be used for nutritional analysis of the diet records using the AusFoods 2019 and AusBrands 2019 databases, including estimated intakes of energy, macronutrients, micronutrients, and food groups [34]. Dietary intake data will be used to compare dietary quality of both study groups at baseline and end-of-program assessments. This includes servings or grams per day of food groups (fruit, vegetables, whole grains, legumes, nuts and seeds, and fish and seafood), fiber, unsaturated oils, and discretionary foods (processed meats, solid fats, added sugars, and alcoholic drinks). To minimize inaccurate self-reporting, participants with implausible intakes of <500 or >3500 kcal/day will be excluded [35].

##### Physical Activity and Sedentary Behavior

The International Physical Activity Questionnaire Short Form (IPAQ-SF) [36] will be used to assess self-reported behavior in the previous week. The survey will be administered by a health professional with experience in physical activity research in an interview setting. Participants will be guided through the questionnaire to gain an understanding of how much time they spend per week being sedentary and performing different intensities of physical activity. IPAQ-SF results will be reported in metabolic equivalent (MET) minutes per week of total activity and minutes per week for sedentary behavior, moderate physical activity, and vigorous physical activity. Heart rate (HR) data from a wearable activity monitor will be used to objectively measure weekly minutes of moderate- to vigorous-intensity physical activity throughout the study. The monitor allows for this intensity range to be preset in a custom heart rate zone. Participants will be provided with information about how to use and synchronize the device at the baseline assessment.

##### Exercise Capacity

The 6-Minute Walk Test (6MWT) will be used to assess exercise capacity. The test will be conducted indoors with temperature control on a 20-meter track under the supervision of a health professional. It will be conducted according to a standardized protocol [37]. The result of the 6MWT will be distance walked, rounded to the nearest meter.

##### Neuromuscular Fitness

The single and repeated chair stand tests will be used to assess functional lower limb neuromuscular strength and endurance. The single chair stand test requires the participant to start in a seated position with the hands crossed against the chest, stand, and then return to a seated posture as quickly as possible. The repeated chair stand test records the time it takes for the participant to complete 5 stands (5xSTS) [37]. One trial will be allotted for this test. The hand grip strength test will be completed using a grip dynamometer 3 times for each hand, with the highest result recorded for both the dominant and nondominant hand. All tests will be conducted under the supervision of a health professional, according to standardized protocols [37].

##### Muscular Pain

Participants will complete the Modified Nordic Musculoskeletal Questionnaire (MNMQ) [38] to quantify musculoskeletal pain. This will be administered via an online form provided by email prior to the baseline and end-of-program assessments.

##### Clinical Parameters

Body mass and height will be measured by a member of the research team with a calibrated weight scale and stadiometer. BMI will be calculated for each participant. Duplicate waist circumference will be measured at a level midway between the lower rib margin and iliac crest in the horizontal plane [37], and the mean will be recorded. If there is a greater than 1.5% difference between waist measures, a third measure will be taken and the median will be recorded [37]. Resting heart rate, systolic blood pressure, and diastolic blood pressure will be measured. Triplicate blood pressure and heart rate measurements will be taken approximately 2 minutes apart, with the participant in a seated position and having rested for at least 10 minutes. Participants will be asked when they last took medication or consumed caffeine. The first blood pressure measurement will be discarded and the mean of the last 2 readings will be used. Biochemical blood analytes will be measured at accredited pathology laboratories (Multimedia Appendix 1).

##### Quality of Life and Self-Efficacy

The EQ-5D-5L scale will be administered via online survey prior to physical assessments and will be used to evaluate quality of life [39]. Four-point validated Likert scales, ranging from 1 (very uncertain) to 4 (very certain), will be used to assess self-efficacy in overcoming barriers related to eating healthy food and carrying out exercise intentions and will be administered under the supervision of a health professional [40].

##### Sleep Quality and Quantity and Fatigue

The Pittsburgh Sleep Quality Index (PSQI) survey will be administered via online survey prior to in-person assessments to quantify sleep quality and duration [41]. Weekly sleep data will be collected using a wearable activity monitor. The monitor records total sleep time and time in sleep stages (deep, light, rapid eye movement, and wakefulness). Participants will be asked to wear the monitor during the night to capture sleep data. The Functional Assessment of Chronic Illness Fatigue Scale (FACIT; version 4) [42] will be administered via online survey prior to in-person assessments to evaluate fatigue.

#### Goal Attainment Score

Goal setting will be facilitated at the baseline assessment for all participants. Participants will be encouraged to set SMART (specific, measurable, achievable, realistic, timely) goals [43]. The goal attainment scaling method will be used to compare goal attainment between the intervention and control groups at end-of-program assessments [44].

#### Treatment Fidelity

Treatment fidelity will be assessed throughout the trial across three areas: training provided, delivery of treatment, and receipt of treatment [45]. Attendance of clinical staff at standardized orientation training and refresher training sessions, as well as regular professional support and case discussions, will be recorded. For delivery of dietetic treatment, the clinicians will summarize the topics covered at the end of each group telehealth session (eg, healthy snacks, vegetables and fruits, and legumes) and the frequency of topics and themes discussed over the course of the project will be described. For delivery of exercise treatment, a record of each training session prescription will be captured.

#### Exposure Demand

Exposure demand will be assessed descriptively by summarizing the frequency of each technology option chosen by the intervention group at baseline and summarizing the different combinations of technologies chosen by the intervention group at baseline.

#### Participant Perceptions

Quantitative and qualitative feedback from participants will be collected at end-of-program assessments. Prior to assessment day, participants will be asked to complete an online questionnaire using a 5-point Likert scale to assess the acceptability of different aspects of the intervention received, its usability, and their satisfaction with it. Quantitative data from the surveys will be analyzed using simple descriptive statistics.

A subsample of participants from both groups will be deliberately selected to achieve maximum demographic diversity for age, sex, and disease group, and they will be invited to provide feedback regarding the model of care received. Semistructured one-on-one interviews will be conducted by a health professional with experience in qualitative research training and no role in delivering the service model. We will interview the participants in-person at the end-of-program assessment visit or via telephone at a time convenient to the participant. Questions will be designed to capture the participant’s impressions of the service model they experienced; potential barriers and facilitators to the diet and exercise recommendations; their perspectives on the technology-assisted delivery methods, usability, and acceptability; and their self-reported intentions for future use of diet monitoring technology after completion of the study period. All interviews will be audio recorded, transcribed verbatim, and thematically analyzed with an iterative and inductive approach.

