### Quantitative Data Collection

Baseline demographic and medical history data that will be collected are listed in Table 1. Research outcomes and the associated measurement methods are outlined in Table 2. Primary outcomes will be assessed once all participants have finished the trial, and secondary outcomes will be collected at baseline and end-of-program assessments. Once a participant is randomized, the research staff will make every reasonable effort (eg, via phone calls, text messages, and emails) to follow the participant for the entire study period for collection of data.

**Table 1 table1:** Demographic and medical data collected prior to the baseline assessment.

Demographic and medical data	Measurements
Sex	Male or female
Date of birth	Date
Ethnicity	Caucasian, Indigenous, European, Anglo-Saxon, Asian, other, unknown/not reported
Marital status	Single or never married, living together, de facto or married, separated or divorced, widowed
Highest education level completed	Primary school, less than grade 10, grade 10, grade 12, vocational school or college, university
Employment status	Full-time, part-time, unemployed, self-employed, student, retired
Medication use	Listed medication intake including type, dose, and frequency
Menopause status	Yes, no, not applicable
Allergies	Yes, no, listed allergies
Cigarette smoking history	Former, current, never
Alcohol consumption	Number of standard drinks per week
Need for assistance to read written health materials^a^	Never, rarely, sometimes, often, always
eHealth literacy	eHealth Literacy Scale (eHEALS)^b^ questionnaire [30]

^a^Assessed through the following question via online form: “How often do you need to have someone help you when you read instructions, pamphlets, or other written material from your doctor or pharmacy?”

^b^eHEALS is a validated 8-question digital health literacy questionnaire that evaluates the ability to find the right type of health information online, where and how to find and use it, possession of the skills and confidence to evaluate the quality of online health information, and the perception of the usefulness and importance of accessing online information for health [30]. This will be administered via an online form.

**Table 2 table2:** Primary and secondary outcomes and their associated measurements.

Outcomes					Measurements

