### All Participants

All participants will receive usual medical and specialist care and may choose to discontinue contact with the health professionals at any time during the study period. All participants will be offered an individualized in-person appointment with a dietitian, review appointments, and a wearable activity monitor. Patients do not currently have access to exercise physiology services as part of standard care.

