### Statistical Analysis

#### Sample Size

As this will be a feasibility study, a sample size calculation was not performed for the primary outcome. To allow for reliable findings, the sample size calculation was conducted using the MetSSS for clinical effectiveness as a secondary outcome. Assuming a correlation of 0.5 between baseline and 26-week MetSSS and an effect size of 0.42 (representing a change of 0.8 in the intervention group and no change in the control group, with a pooled standard deviation of 1.9), the Stata procedure “sampsi” suggests that 67 participants per arm will be required to achieve 80% power to detect a significant difference at the 5% level (2-sided) using an analysis of covariance (ANCOVA). Allowing for 20% dropout, the required number of participants to be recruited will be 168 (84 per arm).

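### Acceptability feedback is timed to the end-of-program assessment and interviewees are not sampled on engagement, so early leavers and low engagers may be under-represented

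*Protocol article*

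**What the plan says.** All of the perceptions data are placed at one time point. Participant Perceptions opens with "Quantitative and qualitative feedback from participants will be collected at end-of-program assessments". The survey on acceptability, usability and satisfaction follows the same timing: "Prior to assessment day, participants will be asked to complete an online questionnaire using a 5-point Likert scale". It is summarized descriptively.

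The interview subsample comes from both groups and is "deliberately selected to achieve maximum demographic diversity for age, sex, and disease group". No other sampling dimension is named. On the interview route the text reads: "We will interview the participants in-person at the end-of-program assessment visit or via telephone at a time convenient to the participant". The topics include barriers and facilitators, usability and acceptability.

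Three other sections bear on who can be reached:

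- All Participants says that participants "may choose to discontinue contact with the health professionals at any time during the study period".
- Quantitative Data Collection says that, after randomization, "the research staff will make every reasonable effort (eg, via phone calls, text messages, and emails) to follow the participant" for the whole study period.
- Sample Size plans for loss: "Allowing for 20% dropout". Under Primary Outcome, the retention criterion is met once at least 70% of intervention participants have an end-of-program assessment.

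**The concern.** The model under test is patient-led, so differences in engagement are part of what is being studied. Attendance and retention figures show how many people left or stopped; they do not show why. The options chosen at baseline, which define exposure demand, cannot show who stopped later. The survey and interviews are where reasons would come out, and Patient and Public Involvement records that patients did not assess the intervention's burden at the design stage.

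If feedback is requested only around the final assessment, people lost before it contribute nothing. If interviewees are diversified on age, sex and disease group alone, those who disengaged but stayed in follow-up enter the interviews only by chance. The account of acceptability and barriers could then lean towards people for whom the program worked well enough to stay. The abstract says that the trial will inform decision-makers on scale and spread, so this evidence will be used.

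**Working it through.** **Inputs from the protocol article.** MetSSS difference 0.8, SD 1.9, baseline to follow-up correlation 0.5, two-sided 5% level, 80% power, 20% dropout, 84 per arm (Sample Size); retention criterion 70% of intervention participants (Primary Outcome).

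**The plan's own figure.** For two means, n = 2 × [(1.96 + 0.842) / (0.8/1.9)]² = 88.5 per arm. The ANCOVA factor is 1 − 0.5² = 0.75, so 88.5 × 0.75 = 66.4, rounded up to 67. Dropout: 67 / (1 − 0.20) = 83.75, rounded up to 84 per arm and 168 in total. The stated sample size is reproduced.

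**Intervention participants without an end-of-program assessment.**

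- At 20% dropout: 84 × 0.80 = 67.2, so about 67 assessed and 84 − 67 = 17 not assessed (20%).
- At the retention threshold: 84 × 0.70 = 58.8, so at least 59 assessed and up to 84 − 59 = 25 not assessed (30%).

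**What that could do to an acceptability proportion.** The documents give no acceptability rates and define no percent-satisfied endpoint, so everything from here on is illustration. Let p be the proportion of assessed participants who rate the program acceptable, q the proportion among those not assessed, m the number not assessed and n = 84. The full-arm proportion is [p(n − m) + qm] / n, and the observed figure exceeds it by (m/n)(p − q).

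Assume p = 80%, that all assessed participants answer, and that nobody else does.

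| Not assessed | Bounds (q = 0 to q = 1) | Overstatement, q = 50% | Overstatement, q = 25% |
|---|---|---|---|
| 17 of 84 | 53.6/84 = 64% to 70.6/84 = 84% | 0.202 × 0.30 = 6 points | 0.202 × 0.55 = 11 points |
| 25 of 84 | 47.2/84 = 56% to 72.2/84 = 86% | 0.298 × 0.30 = 9 points | 0.298 × 0.55 = 16 points |

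With p varied from 70% to 90% and the same q, the overstatement runs from 4 to 13 points (17 missing) or 6 to 19 points (25 missing). The bounds extend above 80% as well as below it: if q exceeds p, the observed figure is too low.

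**Who falls out, from the text.** Stopping contact with the health professionals is not described as leaving the study, and use of the optional components is the participant's choice. Someone who stopped every session remains under the general follow-up commitment and can still be surveyed and interviewed. The group with no stated route is therefore people lost or withdrawn before the final assessment. For disengaged participants who are still followed, the gap is narrower: engagement is simply not a sampling dimension for interviews.

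**The case against.** A reader might infer that everyone who stopped the program is left out and that acceptability is therefore overstated. The documents do not support that. Stopping sessions is not the same as missing the assessment, and staff are committed to pursuing every randomized participant. The survey is online and the telephone interview is an alternative to the visit, so a non-attender could be reached. No sentence restricts feedback to attenders. This stands, and it limits the point to early leavers without a stated route and low engagers who are not deliberately sampled.

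The direction of bias is also unproven. In this population, non-attendance may reflect death or hospitalization, both listed among the serious adverse events, rather than dissatisfaction. The 20% is a sample-size allowance for MetSSS and the 70% is a success threshold; neither is a forecast of survey non-response. This stands too.

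Disengagement is also counted elsewhere: retention, exposure uptake and telehealth adherence are primary outcomes. That is correct, but counts do not supply reasons.

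Finally, an article condenses a fuller protocol, which may contain exit procedures, and sampling for maximum diversity is a recognised qualitative choice. The absence of withdrawal detail alone would be no finding. But the article does state the timing of feedback and does name the sampling dimensions. The point rests on those stated choices: a general promise of follow-up and a telephone option make leavers reachable, yet nothing in the perceptions section directs that they be asked.

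**Conclusion.** The point holds in a limited form. As written, the plan has no stated feedback route for participants lost before the final assessment, and no deliberate interview sampling of those who disengaged. The counts of 17 and 25 assume that the planned dropout, or the retention threshold, is what occurs in the intervention arm.

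Under-representation of these groups is a reasonable expectation. Upward bias in acceptability, and barrier themes drawn too much from those who stayed, are probable rather than shown. The percentage-point figures rest wholly on assumed ratings among people who give no feedback and should not be read as an estimate for this trial.

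The consequence is modest: participant perceptions are a secondary, descriptive outcome, and no feasibility success decision depends on them. The change is still worth making because it costs little.

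**What to change.** 1. Trigger the existing online survey for every randomized participant at week 26, or at withdrawal if earlier, whether or not an assessment is booked, unless consent to contact is withdrawn.
2. Add engagement status to the purposive sampling dimensions, for example: continued, stopped some components, stopped all or withdrew. Offer the telephone interview already planned to those who have stopped.
3. Report survey responses with all randomized participants as the denominator, and separately by engagement status, so that non-response is visible.

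This changes one survey trigger and one sampling frame and needs no new instrument. The downsides are a lower response rate among leavers and possibly a less favourable acceptability figure.

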### All Participants

All participants will receive usual medical and specialist care and may choose to discontinue contact with the health professionals at any time during the study period. All participants will be offered an individualized in-person appointment with a dietitian, review appointments, and a wearable activity monitor. Patients do not currently have access to exercise physiology services as part of standard care.

